#### DURATION:

Subjects will be on study for a total of 4 weeks followed by an additional 48 weeks for safety evaluations.

SAMPLE SIZE: 9 subjects (3 subjects/cohort)

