### 3.0 STUDY DESIGN

This phase I trial is designed to evaluate the safety and immunogenicity of LC002 for the treatment of individuals with chronic HIV-1 infection and HAART-induced durable suppression of viral replication. The study population will include HIV-infected men and women 18 to 50 years of age with a peak plasma HIV-1 RNA > 1000 copies/mL before initiation of HAART. Eligible subjects must have been and remain on a stable HAART regimen (containing drugs of at least two different classes) without changes or interruptions within the 24 weeks prior to study entry and must have a plasma HIV-1 RNA level < 50 copies/mL at least twice within 12 weeks prior to study entry. Subjects should have a CD4+ cell count > 300 cells/mm^3 at the time of entry and a nadir CD4+ cell count > 250 cells/mm^3.

Subjects in cohort 1 will be enrolled to receive one low-dose DermaVir vaccinations (3 subjects). Further enrollment of subjects into the medium and high dose cohorts 2 and 3 (3 subjects, respectively) will begin only after the safety data for cohorts 1 and 2, respectively, are available, and the criteria for enrolling into the next cohort are met (see section 9.1.3). The main criterion to start enrolling the next dose cohort will be the absence of a dose-limiting toxicity in any of the DermaVir subjects in the prior cohort. The actual immunization will be administered once, and after the four-week treatment phase and evaluations, subjects will be followed for an additional 48 weeks for safety.

Subjects will be sequentially enrolled into each cohort:

- Cohort 1:
  - Three subjects will receive a single low-dose vaccination (0.1 mg DNA/subject, 0.8 mL total, administered over two skin sites of 80 cm^2 each, 0.4 mL/site) at study day 0.
- Cohort 2:
  - Three subjects will receive a medium-dose vaccination (0.4 mg DNA/subject, 3.2 mL total, administered over four skin sites of 80 cm^2 each, 0.8 mL/site) at study day 0
- Cohort 3:
  - Three subjects will receive a high-dose vaccination (0.8 mg DNA/subject, 6.4 mL total, administered over eight skin sites of 80 cm^2 each, 0.8 mL/site) at study day 0.

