#### 4.3 Study Enrollment Procedures

4.3.1 Prior to implementation of this protocol, the protocol and consent form must be approved by the local institutional ethics committee.

Once a candidate for study entry has been identified, details will be carefully discussed with the subject. The subject (or parent or legal guardian if the subject is under guardianship) will be asked to read and sign the consent form.

Only subjects who meet the eligibility criteria at both the screening and pre-entry visits will be enrolled. Cohorts will enroll serially. After all 3 subjects of a given cohort (#1 or #2) have received their study vaccine administrations, and have remained on study through at least the 14th day, if no subject in any cohort has experienced a Primary Safety endpoint (defined in section 9.2.1), then the study will dose escalate by opening enrollment of subjects into the next cohort.

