#### 9.1.3 Dose Escalation Rule

Dose escalation will occur if

- 1) at least 2 subjects were on study until at least 14 days after receiving their study vaccination and
- 2) no subject in the current or lower dose cohort experienced a Primary Safety Endpoint.

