### 9.2 Endpoints

#### 9.2.1 Primary endpoint: Safety

Occurrence of at least one grade 3 or higher adverse event including signs/symptoms, lab toxicities and clinical events that is "possibly, probably," or "definitely" related to study treatment (as judged by the Principal Investigator, including site clinicians on the team) any time from the first day of study treatment until 28 days after LC002 administration.

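### The next dose cohort may open after a 14-day minimum, but the safety endpoint that must be absent runs to Day 28, and no rule covers an endpoint on Days 15-28 once the next cohort is open

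*Protocol*

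**What the plan says.** **Escalation rule (Protocol 9.1.3).** There are two conditions. The first is that two or more subjects stayed on study "until at least 14 days after receiving their study vaccination". The second is that "no subject in the current or lower dose cohort experienced a Primary Safety Endpoint". Only the first carries a day.

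**Enrolment procedures (Protocol 4.3).** The same decision is described for all three subjects of a cohort: they must "have remained on study through at least the 14th day, if no subject in any cohort has experienced a Primary Safety endpoint". Once this is met, the study escalates by opening enrolment into the next cohort.

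**The endpoint (Protocol 9.2.1).** A subject has a Primary Safety Endpoint with at least one adverse event of grade 3 or higher judged at least possibly related to study treatment, "any time from the first day of study treatment until 28 days after LC002 administration".

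**Study design (Protocol 3.0).** Enrolment into the medium and high dose cohorts "will begin only after the safety data for cohorts 1 and 2, respectively, are available". No day is given, and the reader is sent to 9.1.3 for the criteria. Section 3.0 and the Schema name the absence of a dose-limiting toxicity as the main criterion. That term is not defined anywhere, so the working rule is the one in 9.1.3 and 4.3.

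**The concern.** The rule asks for the absence of an endpoint at a time when that endpoint may not be fully observed. On Day 14 a subject can only be said not to have failed yet. A related grade 3 or higher event on Days 15-28 could then appear after the next cohort has opened, so subjects could be given a higher dose although the dose below goes on to fail the protocol's own criterion. This rule is the main protection for subjects in a first-in-human escalation with three subjects per dose, and the endpoint in question is the trial's primary endpoint.

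**Working it through.** The protocol states no power, error rate or escalation probability, so there is no figure of its own to reproduce. The point rests on the text; the probabilities only show its possible size.

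**1. Unobserved part of the window.** Follow-up required: at least 14 days (9.1.3, 4.3). Endpoint window: 28 days (9.2.1). For a subject with exactly 14 days of follow-up, (28 - 14)/28 = 50% of the window is still to come. Of the three scheduled post-vaccination visits in the treatment phase (Days 7, 14 and 28; section 6.1), one is still to come.

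**2. Number of subjects.** Section 4.3 requires 14 days from all three; section 9.1.3 requires it from two. Under 9.1.3 the third subject may have less than 14 days, so more than half of that subject's window can be open.

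**3. What the look-back catches.** Condition 2 covers lower cohorts.
- *Cohort 1 event on Days 15-28.* It may come after Cohort 2 has opened. Under 4.3, Cohort 1 subjects have at least 14 days when Cohort 2 opens, and Cohort 2 subjects need at least 14 more before Cohort 3 opens. Cohort 1 is then at 14 + 14 = 28 days or later, so the event, if known by then, blocks Cohort 3. It cannot undo dosing already given in Cohort 2.
- *Cohort 2 event on Days 15-28.* It may come after Cohort 3 has opened, and no escalation decision remains.

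**4. Replacement rule (9.3).** A subject who leaves before the Week 4 evaluation without an endpoint, for reasons unrelated to vaccination, is replaced. Someone leaving on Day 20 would have counted towards escalation and would still need replacing. The protocol thus uses two follow-up standards without saying so.

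**5. Illustration.** Inputs: n = 3 per cohort (Schema: "9 subjects (3 subjects/cohort"). Section 9.1 speaks of 9 per cohort, but the Schema and sections 3.0, 4.3 and 5.1.1 all give 3. Assumed, not in the protocol: p, the 28-day endpoint risk per subject, and s, the share of that risk falling by Day 14.

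- No endpoint over 28 days: (1 - p)^3
- No endpoint seen at exactly 14 days: (1 - s·p)^3
- The difference is the chance that the next cohort opens and the lower cohort later has an endpoint.

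| p | Full 28 days | s = 90% | s = 75% | s = 50% | s = 25% |
|---|---|---|---|---|---|
| 0.10 | 72.9% | 75.4% | 79.1% | 85.7% | 92.7% |
| 0.20 | 51.2% | 55.1% | 61.4% | 72.9% | 85.7% |
| 0.33 | 30.1% | 34.7% | 42.6% | 58.2% | 77.2% |

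For example, at p = 0.33 and s = 75%: (1 - 0.2475)^3 = 0.7525^3 = 0.426, against 0.67^3 = 0.301, a difference of 12.5 points. At p = 0.33 the differences across the row are 4.7, 12.5, 28.1 and 47.2 points.

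In the limiting case under 9.1.3, the third subject contributes no follow-up and the exponent is 2. At p = 0.33 the chance of seeing no endpoint is then 49.4%, 56.6%, 69.7% or 84.2% for the same four values of s.

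**The case against.** Several stronger readings are tempting, and the text does not support them.

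- *The rule reads the endpoint on Day 14.* Both sections set 14 days as a minimum, and condition 2 has no Day 14 cut-off. Any endpoint known when the decision is made counts, and subjects vaccinated earlier may have longer follow-up. The 50% is the position at the earliest permitted decision.
- *No later decision catches a late event.* This can be said only of a Cohort 2 event after Cohort 3 has opened. The look-back would stop Cohort 3 for a known late event in Cohort 1.
- *Section 3.0 is false.* It speaks of safety data, not of the completed primary endpoint. It is vague.
- *Day 28 autoantibody and HIV-1 RNA results are part of the unobserved endpoint.* Neither has a row in the Appendix IV grading table, and a post-vaccination RNA is already taken on Day 7. They add little here.

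Three further points count for the plan. Opening enrolment is not dosing: screening, pre-entry and entry visits come first, with at least 24 hours between successive visits (6.2.1, 6.2.2), so part of the open window may pass before a higher dose is given. General safeguards exist: contact with the Principal Investigator within 48 hours for related non-local grade 3 or 4 reactions (7.1.2), 24-hour reporting of serious events (10.4), and the power to discontinue the study at any time (11.3). And after one three-hour topical application most events may come early; local reactions in the animal studies were mild and transient (2.2). At s = 90% the excess at p = 0.33 is only about 5 points.

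All this limits the size of the problem. It does not remove the mismatch: nothing requires Day 28 data first, and none of the safeguards says how a late endpoint acts on an open cohort.

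**Conclusion.** The point stands as a mismatch between sections together with a missing rule. Sections 9.1.3 and 4.3 permit escalation after a 14-day minimum on the absence of an endpoint that 9.2.1 defines to 28 days, and they disagree on whether two or three subjects must reach that minimum. Up to 14 of 28 endpoint days are unobserved for a subject with exactly 14 days, and more for a third subject under 9.1.3. The exposure is greatest for a late event in Cohort 2.

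How often this would matter cannot be derived from the protocol. At an assumed 28-day risk of 33%, the chance of seeing no endpoint at the decision rises from 30% to between 35% and 77%, depending on event timing. Those figures assume independent subjects, three per cohort, and a decision at exactly 14 days for each. They do not show that late toxicity is expected. Because the rule governs subject safety and the correction is cheap, it should be made.

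**What to change.** Reconcile sections 3.0, 4.3, 9.1.3 and 9.2.1 by amendment:

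1. Make the escalation decision and the safety endpoint it names cover the same stated period, or say plainly that the decision rests on incomplete endpoint data. The choice of period is the sponsor's.
2. State one number of subjects who must reach that period, the same in 4.3 and 9.1.3.
3. State how a Primary Safety Endpoint on Days 15-28 acts on a higher cohort already open.
4. In 3.0, say which safety data must be available, and through which day.

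The cost is amendment wording. If the two windows are made equal, the delay is up to 28 - 14 = 14 days per escalation, or about four weeks over the two escalations. No visits are added, because Day 28 is already in the schedule of events.

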### 9.2 Endpoints

#### 9.2.1 Primary endpoint: Safety

Occurrence of at least one grade 3 or higher adverse event including signs/symptoms, lab toxicities and clinical events that is "possibly, probably," or "definitely" related to study treatment (as judged by the Principal Investigator, including site clinicians on the team) any time from the first day of study treatment until 28 days after LC002 administration.

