### 4. Post-treatment phase – evaluations after Day 28 (safety follow up):

- a. Medication history at Weeks 12, 24, 36, 48.
- b. Targeted physical examination at Weeks 12, 24, and 36.
- c. Complete physical examination at Week 48.
- d. Hematology evaluations at Weeks 12, 24, 36 and 48.
- e. Blood chemistries and liver function tests at Weeks 12, 24, 36 and 48.
- f. Autoantibodies (ANA, anti-ds-DNA) at Week 48.
- g. Urinalysis at Weeks 12, 24, 36 and 48.
- h. HIV-1 RNA at Weeks 12, 24, 36 and 48.
- i. CD4/CD8 count at Weeks 12, 24, 36 and 48.

- j. Plasma and PBMCs for storage at Weeks 12, 24, 36 and 48.

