### 7.2 Antiretroviral Drugs

Unanticipated and anticipated toxicities from the HAART regimen will be graded according to the Division of AIDS Table for Grading Adult Adverse Experiences (see Appendix IV). Any Grade 3 or 4 toxicities that result in a temporary or permanent change in an antiretroviral therapy must be reported to the Principal Investigator.

Anticipated toxicities resulting from components of the HAART regimen will be managed by the subject's clinician according to best clinical practice including dose reductions when indicated.

If the HIV-1 viral load becomes detectable (plasma HIV-1 RNA > 1,000 copies/mL) either during the treatment phase (Day 0 to 28) or 48-week follow up, it should be repeated one week later and compliance issues should be ruled out. If the repeated HIV-1 viral load is detectable (plasma HIV-1 RNA > 1,000 copies/ml) genotyping should be performed and HAART changed if necessary.

In case of virologic failure, genotyping will also be performed on the nef gene. As the nef gene contained in the DNA of LC002 is truncated, detection of a truncated nef gene would indicate recombination of the patient's virus with the vaccine. All patients with virologic failure will be followed for the complete 48-week follow up period.

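### The escalation rule in 9.1.3 and 4.3 is not held by a truncated-nef result from a draw after Day 28, or by a virologic-failure work-up under 7.2 that is still open at the gate

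*Protocol*

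**What the plan says.** **Looking for recombination (Protocol 7.2).** If HIV-1 RNA exceeds 1,000 copies/mL, "either during the treatment phase (Day 0 to 28) or 48-week follow up, it should be repeated one week later", with compliance checked. If the repeat is also above 1,000 copies/mL, resistance genotyping follows, and HAART is changed if necessary. In virologic failure nef is genotyped too, because "detection of a truncated nef gene would indicate recombination" between the patient's virus and the vaccine. The section then requires the full 48 weeks of follow-up for that patient. It says nothing about dosing other subjects.

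**When RNA is drawn (Protocol 6.0).** Draws after vaccination are on Days 7 and 28, then "HIV-1 RNA at Weeks 12, 24, 36 and 48".

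**What decides escalation.** Section 9.1.3 begins "Dose escalation will occur if" and lists two conditions: at least 2 subjects on study to 14 days, and "no subject in the current or lower dose cohort experienced a Primary Safety Endpoint". Section 4.3 asks that all 3 subjects "have remained on study through at least the 14th day", and continues: "if no subject in any cohort has experienced a Primary Safety endpoint (defined in section 9.2.1), then the study will dose escalate". The endpoint in 9.2.1 is a grade 3 or higher adverse event judged possibly, probably or definitely related, occurring "any time from the first day of study treatment until 28 days after LC002 administration".

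**Other relevant text.** The Schema and section 3.0 require safety data from the prior cohort to be available and call absence of dose-limiting toxicity the main criterion; 3.0 refers to 9.1.3 for the criteria. Section 11.3 lets several parties discontinue the study at any time.

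**The concern.** Recombination is the vaccine-specific harm that 7.2 is written to detect, and 7.2 looks for it for much longer than the escalation rule does. The conditions in 9.1.3 and 4.3 are worded as sufficient: once they are met, escalation follows. A truncated-nef result from a draw after Day 28 lies outside the endpoint whatever its grade or relatedness. An unfinished work-up is not an endpoint event either.

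At stake is the next dose step, from 0.1 to 0.4 mg DNA or from 0.4 to 0.8 mg. New subjects could be exposed to it after recombination has been found in a lower cohort, or while the test for it is pending. Section 2.1 states that the plasmid modifications eliminate the risk of replication-competent virus emerging by recombination. A positive result should therefore be rare, but it would contradict the premise on which the higher dose is given.

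**Working it through.** The protocol gives no figure on this point to reproduce. The check compares dates.

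**Inputs.** RNA draws on Days 7 and 28 and Weeks 12, 24, 36 and 48 (6.0); repeat one week later (7.2), taken as 7 days; gate at 14 days (9.1.3, 4.3); endpoint window 28 days (9.2.1); visit window ±3 days (6.2.2). Assumptions: genotyping takes 0 to 14 days, and weeks are counted from immunization, as 6.2.5 suggests.

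**When Cohort 3 can open.** Count from the first Cohort 1 dose and use the stricter form in 4.3 (all 3 subjects). Let *a* be the days from the first to the last Cohort 1 dose, and *b* the days from the opening of Cohort 2 to its last dose. The Cohort 3 gate is then at *a* + 14 + *b* + 14 = 28 + T, where T = *a* + *b* is the combined enrolment time for 6 subjects. The protocol does not state T.

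**Late finding, first Cohort 1 subject.** The repeat precedes the Cohort 3 gate if draw day + 7 ≤ 28 + T.

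| Draw | Repeat | T needed (days) |
|---|---|---|
| Week 12 (Day 84) | Day 91 | 91 − 28 = 63 |
| Week 24 (Day 168) | Day 175 | 175 − 28 = 147 |
| Week 36 (Day 252) | Day 259 | 259 − 28 = 231 |
| Week 48 (Day 336) | Day 343 | 343 − 28 = 315 |

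- With 14 days for genotyping, Week 12 needs T = 63 + 14 = 77 days.
- If Week 12 is counted from Day 28, the draw is on Day 112 and the repeat on Day 119. T is then 119 − 28 = 91 days, or 105 with genotyping.
- For the last-dosed Cohort 1 subject, *b* alone must be at least 63 days.
- For the first Cohort 2 subject, dosing of that cohort must span at least 91 − 14 = 77 days.
- With no accrual delay (T = 0), Cohort 3 opens on Day 28, before any follow-up RNA draw, and this case cannot arise.

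The gate opens enrolment, so a finding can precede Cohort 3 dosing at a somewhat smaller T.

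**Open work-up.** For the last-dosed subject of a cohort, a Day 7 rebound is repeated on Day 7 + 7 = 14, or between Days 4 + 7 = 11 and 10 + 7 = 17 with the visit window. The gate can be met on Day 14. Nef genotyping, if the rebound is confirmed, comes after that. This case does not depend on slow accrual. Subjects dosed earlier have more time.

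**How often a hold might occur.** If a fraction *p* of subjects had an RNA above 1,000 copies/mL before Cohort 3 opens, the chance of at least one hold among 6 is 1 − (1 − *p*)^6. For *p* = 0.01 this is 0.059, and for *p* = 0.05 it is 0.265, so about 6% to 26%. The range for *p* is assumed; the protocol gives no rate.

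**The case against.** **Section 7.2 guides individual care under HAART toxicity and is not a monitoring programme.** This is right as far as it goes. A reader might infer that recombination is tested routinely for 48 weeks. It is not: nef is genotyped only after a confirmed RNA above 1,000 copies/mL. The section still states what a positive result would mean, and the escalation rule has no place for it.

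**Four of the six draws after vaccination fall outside the endpoint window.** A reader might take that as the size of the gap. It overstates it, because only results known before Cohort 3 is dosed can affect escalation. That leaves, realistically, Week 12 in a Cohort 1 subject.

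**The Schema and 3.0 leave room for judgement.** Main criterion is not only criterion, and safety data must be available. It is not natural to read the protocol as intending escalation after proven recombination, and that intention should not be attributed to it. But 3.0 refers to 9.1.3, which lists two conditions, and no further criterion is written anywhere.

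**Events within 28 days can already count.** This stands. The general severity scale in Appendix IV and its rule for serious events let a clinician grade a rebound or recombination at 3 or higher. The documents do not support a claim that the endpoint ignores recombination altogether.

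**Any fixed safety window misses late events, and 11.3 covers them.** A short window is a legitimate choice, and this point does not dispute it. The power in 11.3 is discretionary, however, and concerns stopping the study, whereas 9.1.3 and 4.3 direct escalation.

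**The open-work-up case is thin.** It bites mainly for a late-dosed subject with a Day 7 rebound. New subjects also need evaluations at least 24 hours apart (6.2.1, 6.2.2), which gives some time. Neither 9.1.3 nor 4.3 makes dosing wait for the result.

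**Conclusion.** The point holds in a narrow form. Under 9.1.3 and 4.3 as written, neither a truncated-nef result from a draw after Day 28 nor a 7.2 work-up open at the gate holds escalation.

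The late case needs a confirmed rebound, truncated nef and slow enrolment: about 63 to 77 days for Cohorts 1 and 2 together, or 91 to 105 if Week 12 is counted from Day 28. Strict eligibility in 4.1 makes nine weeks for six subjects plausible, but accrual time is not stated and the case may never arise. The open case needs only an early rebound in a late-dosed subject.

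A reader might conclude that any truncated nef should end escalation outright. The documents do not support that. No baseline nef genotype is scheduled, so nothing planned would separate a truncation already present from recombination. A hold for review is the proportionate response.

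Severity is low to moderate: the event is expected to be rare, but the rule gives the wrong direction if it occurs.

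**What to change.** Add to both 9.1.3 and 4.3:

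1. No subject in the next cohort is dosed while a 7.2 work-up (repeat test, compliance check and, if confirmed, nef genotyping) is open in a current or lower cohort.
2. A truncated-nef finding in a current or lower cohort, whenever detected, holds escalation until the Principal Investigator and sponsor have reviewed it and documented that it is not vaccine recombination, for example by comparison with the pre-entry PBMC already stored under 6.1. If recombination is not excluded, escalation does not proceed.

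Leave 9.2.1 unchanged. Leave a confirmed rebound with intact nef to the existing grading and relatedness judgement.

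The RNA draws, repeat test, compliance check and nef genotyping are already planned. The comparison with stored PBMC would be extra laboratory work, needed only after a truncated-nef finding. The cost of the first addition is a delay of about 7 days if the repeat is not above 1,000 copies/mL, and longer if genotyping follows. That includes rebounds caused by missed HAART doses. The second adds a delay for review, or a stop if recombination cannot be excluded.

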#### Signs and Symptoms

At study entry, all signs/symptoms must be recorded. On study, any signs or symptoms that led to a change in treatment, regardless of grade, must be recorded in the CRFs. Record all grades of local reactions and any other signs or symptoms Grade 2 or higher in the CRFs.

All signs, symptoms, HIV-related and AIDS-defining events, deaths, and

toxicities must be documented, and must be recorded in the CRFs within 48 hours throughout the course of the study.

Refer to the Division of AIDS Table for Grading Adult Adverse Experiences for toxicity grading.

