#### 6.4 Off-Drug Requirements

Additional 12-week period safety monitoring and reporting of serious adverse experiences (SAEs) continues to be required upon completion or discontinuation of study treatment regardless of whether a protocol follow-up period is scheduled to occur. After 12 weeks OFF study treatment, there are four types of events that must be reported if the relationship to the study drug is assessed by the site physician as definitely, possibly, or unable to judge: DEATHS, NEW ONSET CANCERS, CONGENITAL ANOMALIES, AND PERMANENT DISABILITIES.

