#### 7.1.2 Systemic reactions

Systemic reactions will be graded according to the Division of AIDS Table for Grading Adult Adverse Experiences (see Appendix IV). The Principal Investigator should be contacted within 48 hours for any non-local Grade 3 or 4 reactions (for example, elevated temperatures following immunization) thought definitely, possibly, or probably related to vaccination with LC002.

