### 11.3 Study Discontinuation

The study may be discontinued at any time by the Local Ethical Committee, the Principal Investigator, the pharmaceutical sponsor(s), the NIP, or other government agencies as part of their duties to ensure that research subjects are protected.

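### The escalation rule looks back to lower cohorts only through an endpoint that closes at Day 28, so a later related Grade 3+ event in Cohort 1, even if known, does not fail the criterion for opening Cohort 3

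*Protocol*

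**What the plan says.** Section 9.1.3 sets two conditions for escalation. At least two subjects must have been on study to Day 14 after vaccination, and the safety condition is that "no subject in the current or lower dose cohort experienced a Primary Safety Endpoint". Section 4.3 asks for all three subjects to reach Day 14 and continues: "if no subject in any cohort has experienced a Primary Safety endpoint (defined in section 9.2.1), then the study will dose escalate".

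Section 9.2.1 defines that endpoint as at least one Grade 3 or higher adverse event judged possibly, probably or definitely related, occurring "any time from the first day of study treatment until 28 days after LC002 administration".

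Section 3.0 words its main criterion differently, as the "absence of a dose-limiting toxicity in any of the DermaVir subjects in the prior cohort", and sends the reader to 9.1.3 for the criteria. The schema also names absence of a dose-limiting toxicity as the main criterion. Neither place defines the term.

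Safety information is collected well past Day 28. Follow-up runs to Week 48. Section 6.4 states: "Additional 12-week period safety monitoring and reporting of serious adverse experiences (SAEs) continues to be required". Under Signs and Symptoms in 6.3.6, toxicities "must be recorded in the CRFs within 48 hours throughout the course of the study". Section 7.1.2 says the Principal Investigator "should be contacted within 48 hours for any non-local Grade 3 or 4 reactions" thought related to the vaccine. Section 11.3 adds a general power: "The study may be discontinued at any time".

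**The concern.** A Day 28 cut-off is reasonable for a fixed primary endpoint. In 9.1.3 and 4.3 the same endpoint does a second job: it is the cumulative look-back to lower cohorts. By the time Cohort 3 opens, Cohort 1 may have been followed for longer than 28 days, and the look-back ignores everything in that extra time.

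The consequence is concrete. Suppose a Cohort 1 subject has a related Grade 3 event on Day 35 and it is reported before Cohort 3 opens. No Primary Safety Endpoint has occurred, so the written conditions for moving three new subjects to 0.8 mg are still met. Cohort 1 received 0.1 mg, and 0.8 / 0.1 = 8. The information would be in hand; the criterion simply does not use it.

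**Working it through.** **1. Does the text let a late event through?** Take a related Grade 3+ event in Cohort 1 on Day 35, known when Cohort 3 is due to open.

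- 9.2.1: Day 35 is after Day 28, so it is not a Primary Safety Endpoint.
- 9.1.3 condition 2 and 4.3: both test only for that endpoint, so both are still satisfied.
- 3.0: the prior cohort at this decision is Cohort 2, so a Cohort 1 event is not reached, and 3.0 refers back to 9.1.3.
- Schema: dose-limiting toxicity carries no time limit and no cohort limit, but it is undefined.
- 11.3: the study may be stopped, but by discretion; this is not part of the criterion.

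**2. How much follow-up is uncovered?** The protocol gives no accrual rate and no figure on this point to reproduce. The inputs are three subjects per cohort (schema, 3.0, 5.1.1), 14 days before the next cohort opens (4.3, 9.1.3) and a 28-day window (9.2.1). The one assumption is R, the weeks taken to dose a cohort, with doses at 0, R/2 and R and no lag between opening a cohort and its first dose.

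*Under 4.3 (all three subjects to Day 14).* Cohort 2 opens at R + 2 and its last dose is at 2R + 2. Cohort 3 opens at 2R + 4. Cohort 1 follow-up is then 2R + 4, 1.5R + 4 and R + 4, in total 12 + 4.5R. The window covers 3 × 4 = 12, leaving 4.5R outside.

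*Under 9.1.3 (two subjects to Day 14).* Cohort 2 opens at R/2 + 2 and its second dose is at R + 2. Cohort 3 opens at R + 4. Cohort 1 follow-up is R + 4, R/2 + 4 and 4, in total 12 + 1.5R, leaving 1.5R outside.

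| R (weeks, assumed) | 4.3: Cohort 3 opens | 4.3: outside / total | 9.1.3: Cohort 3 opens | 9.1.3: outside / total |
|---|---|---|---|---|
| 0 | week 4 | 0 / 12 = 0% | week 4 | 0 / 12 = 0% |
| 1 | week 6 | 4.5 / 16.5 = 27% | week 5 | 1.5 / 13.5 = 11% |
| 2 | week 8 | 9 / 21 = 43% | week 6 | 3 / 15 = 20% |
| 4 | week 12 | 18 / 30 = 60% | week 8 | 6 / 18 = 33% |
| 8 | week 20 | 36 / 48 = 75% | week 12 | 12 / 24 = 50% |

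In days, R = 2 (doses 7 days apart) leaves the three Cohort 1 subjects 28, 21 and 14 uncovered days under 4.3, and 14, 7 and 0 under 9.1.3. A 14-day lag before Cohort 2's first dose adds 14 days to each of these.

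**3. Would anyone see a late event?** After Day 28 the next scheduled visit is Week 12. Apart from Day 28 visits made up to three days late (6.2.2), the uncovered time holds no scheduled visit for R up to 2. Under 4.3 it holds at most one at R = 4 (first subject at week 12) and at most three at R = 8 (subjects at weeks 20, 16 and 12). Under 9.1.3 the counts are none at R = 4 and at most one at R = 8. Late events would mostly become known through SAE or unscheduled reports. SAE monitoring under 6.4 lasts 12 weeks, at least 12 − 4 = 8 weeks beyond the endpoint window.

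**The case against.** The best defence is that 9.1.3 is not the only safeguard. The schema and 3.0 open the next cohort only once safety data are available, and call absence of a dose-limiting toxicity the main criterion, not the sole one. SAEs go to the authority and the sponsor's representative within 24 hours (10.4), and several bodies may stop the study under 11.3. A fixed toxicity window backed by discretion can be called a design choice. This stands in part. A reader might infer that nothing could stop the 0.8 mg dose; the documents do not support that. What they show is that the stop depends on judgement or on an undefined term, while the rule that was written to look back does not reach the event.

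Three further readings go too far:

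- That the protocol expects late related events. Section 6.4 requires monitoring, which is not an expectation. Section 2.1 says PEIm with DNA is not expected to cause significant toxicity in humans.
- That the 4.3 shares are the size of the gap. They hold only if all three subjects must reach Day 14; the two-subject condition in 9.1.3 gives smaller ones.
- That vaccine recombination shown by a truncated nef gene (7.2) can never count. Section 9.2.1 does not name it and Appendix IV has no HIV-1 RNA row. A clinician can still grade it on the estimation scale, or as Grade 4 if it is a clinical event deemed serious. That issue is separate and does not turn on Day 28.

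**Conclusion.** The gap is real and narrow. As written, a related Grade 3+ event in Cohort 1 after Day 28, known before Cohort 3 opens, does not fail 9.1.3 condition 2 or the matching condition in 4.3. This follows from the text and needs no assumption.

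Its size does need one. The uncovered time is zero if each cohort is dosed on a single day without delay, and otherwise grows with accrual time and lag. For R from 1 to 8 weeks it is 27% to 75% of Cohort 1 subject-weeks under 4.3, or 11% to 50% under 9.1.3. R is assumed, and these shares say nothing about how likely a late event is. The discretionary stop in 11.3 keeps this from being a more serious fault. An amendment is still warranted, because the rule is meant to act on harm in lower cohorts and the information is already being collected.

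**What to change.** Keep 9.2.1 unchanged. Reword 9.1.3 condition 2, and 4.3 to match:

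> No subject in the current or any lower dose cohort has, up to the date of the escalation decision, had a Primary Safety Endpoint or any other Grade 3 or higher event judged possibly, probably or definitely related to LC002.

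This adds no visits or subjects, only one cumulative review of CRF and SAE data before each cohort opens.

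There are two costs. One late related event would bar escalation, as one by Day 28 already does. Slower accrual would also lengthen the look-back and so raise the chance of a stop. If q is an assumed per-subject risk of a related Grade 3+ event in the uncovered time, the chance of at least one among three Cohort 1 subjects is 1 − (1 − q)³: 3.0% at q = 1%, 14.3% at 5% and 27.1% at 10%. Under the present criterion such an event blocks with probability zero.

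A separate, optional addition is to name confirmed truncated-nef recombination under 7.2 as a blocking event, so that it does not rest on clinician grading.
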